Subjects will be fasted, will avoid caffeine (Section 7.1.3), and will not smoke (Arms A, B, and D) for 2 hours prior to collection of blood samples.

The exact volumes of each sample may change but the total volume of blood drawn for any subject will not exceed 400 mL.

- 1. Other Study Assessments
     1. Physiological Assessments
        1. Body Weight and Waist Circumference

Body weight in underclothing and without shoes and waist circumference will be measured at the timepoints indicated in the Schedule of Assessments (Appendix 15.1).

- - - 1. Augmentation Index and Carotid/Femoral Pulse Wave Velocity

Augmentation index and carotid/femoral pulse wave velocity assessments will be conducted at the timepoints indicated in the Schedule of Assessments (Appendix 15.1) using a SphygmoCor XCEL device according to the manufacturer’s instructions.

Prior to measurements, subjects will fast and avoid caffeine for 4 hours (described in Section 7.1.3, and will not smoke (Arms A and B) for 2 hours. Subjects will have rested for 10 minutes in a supine position prior to measurements.

- - - 1. 6-minute Walking Test

A 6-minute walking test will be conducted at the timepoints indicated in the Schedule of Assessments (Appendix 15.1) in accordance with the European Respiratory Society/American Thoracic Society guidelines.^23^

Subjects will be asked to walk the greatest distance they can in 6-minutes without jogging or running. Subjects will be instructed to wear appropriate clothing, and will be monitored throughout the test by a suitably qualified member of staff. Subjects are permitted to eat a light meal prior to the test occurring, and will be required to rest in a seated position for 10 minutes prior to the start of the test. During the test, subjects will regulate their pace, and can slow down or stop if required. Subjects blood oxygen saturation levels (SpO_2_) will be monitored continually during the 6-minute walking test using a wrist-mounted pulse oximeter.

- - - 1. Finger Plethysmography

Finger plethysmography will be conducted at the timepoints indicated in the Schedule of Assessments (Appendix 15.1) using an EndoPAT^TM^ device and software according to the manufacturer’s instructions.

Subjects will be fasted, will avoid caffeine (Section 7.1.3), and will not smoke (Arms A, B, and D) for at least 2 hours prior to measurements. Subjects will have rested for 10 minutes in a supine position prior to measurements.

- - 1. Questionnaires

A paper copy of the subject questionnaires used in this study will be completed by each subject, and the Investigator/clinical site staff will review each questionnaire for completeness. Subjects will be required to answer all questions on each questionnaire. Questionnaires will be provided in English.

- - - 1. Tobacco Use History (All Subjects)

A tobacco use history questionnaire will be administered to all subjects at Screening only.

- - - 1. Fagerström Test for Cigarette Dependence (Arms A, B, and D Only)

Potential nicotine dependence will be assessed via a questionnaire at Screening and the study visits indicated in the Schedule of Assessments (Appendix 15.1) using a **FTCD questionnaire in its revised version.**^24^

**The questionnaire consists of 6 questions which will be answered by the subject himself/herself. The scores obtained on the test permit the classification of nicotine dependence into 3 levels: Mild (0-3 points), moderate (4-6 points), and severe (7‑10 points).**

- - - 1. Product Satisfaction (Arms A and B Only)

The Product Satisfaction questionnaire will be administered to subjects at the study visits indicated in the Schedule of Assessments (Appendix 15.1).

The questionnaire consists of 1 question, “Can you tell me how much do you like this tobacco product?” which will be answered by the subject himself/herself. The subject will provide responses on a 7-point Likert scale ranging from “1 – I dislike it a lot” to “7 – I like it a lot” (scores of 2 – 6 will not have a descriptor).

- - - 1. Smoking Cessation Quality of Life (Arms B and D only)

The impact of smoking cessation on perceived functioning and well-being will be assessed via a questionnaire administered to subjects at the study visits indicated in the Schedule of Assessments (Appendix 15.1), using the Smoking Cessation Quality of Life questionnaire.^25^

The Smoking Cessation Quality of Life questionnaire contains 5 multiple-item cessation‑targeted scales: social interactions, self-control, sleep, cognitive functioning and anxiety.

- - - 1. Cough and Shortness of Breath (All Subjects)

Cough and shortness of breath will be assessed using a visual analog scale (VAS) at the visits indicated in the Schedule of Assessments (Appendix 15.1).

- - - 1. Product Use Count (Arms A, B, and D Only)

The number of conventional cigarettes smoked or products used will be recorded daily between Days 1 and 360 using an eDiary. If the eDiary is not able to be used, subjects will record cigarette or product use using a paper diary.

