| Total nicotine equivalents (nicotine, cotinine, 3-hydroxycotinine and their glucuronide conjugates) | TNeq | Nicotine | Urine  (24-hour) * |
| Total N-nitrosonornicotine | Total NNN | NNN | Urine  (24-hour) * |
| 3-hydroxypropylmercapturic acid | 3-HPMA | Acrolein | Urine  (24-hour) * |
| 3-hydroxy-1-methylpropylmercapturic acid | HMPMA | Crotonaldehyde | Urine  (24-hour) * |
| S-phenylmercapturic acid | S-PMA | Benzene | Urine  (24-hour) * |
| [Monohydroxybutenyl-mercapturic acid](http://onlinelibrary.wiley.com/doi/10.1002/3527600418.bi10699e0011/pdf) | MHBMA | 1,3-butadiene | Urine  (24-hour) * |
| 2-cyanoethylmercapturic acid | CEMA | Acrylonitrile | Urine  (24-hour) * |
| 1-hydroxypyrene | 1-OHP | Pyrene | Urine  (24-hour) * |
| 2-hydroxyethylmercapturic acid | HEMA | Ethylene oxide | Urine  (24-hour) * |
| 4-aminobiphenyl | 4-ABP | 4-aminobiphenyl | Urine (24‑hour) * |
| 2-aminonaphthalene | 2-AN | 2-aminonaphthalene | Urine (24‑hour) * |
| Ortho-toluidine | o-Tol | Ortho-toluidine | Urine (24‑hour) * |

| **Biomarker of Compliance** | | **Abbreviation** | **Indication** | **Matrix** |
| --- | --- | --- | --- | --- |
| N-(2-cyanoethyl)valine (haemoglobin adduct) † | | CEVal | Acrylonitrile | Whole blood |
| **Biomarker of Biological Effect** | | **Abbreviation** | **Indication** | **Matrix** |
| Nitric oxide | | NO | Bronchodilation/vascular tone | Exhaled breath |
| 11-dehydrothromboxane B2 | | 11-dTx B2 | Platelet activation/coagulation | Urine  (24-hour) * |
| 4-hydroxy-nonenal + metabolites | | 4-HNE | Oxidative stress | Urine  (24-hour) * |
| White blood cell count | | WBC count | Inflammation | Whole blood |
| Monocyte chemotactic protein 1/ C-C motif chemokine ligand 2 | | MCP-1/CCL2 | Inflammation/chemokine | Plasma |
| Soluble intercellular adhesion molecule-1 | | s-ICAM1 | Endothelial dysfunction | Plasma |
| Fibrinogen | | Fib | Coagulation | Plasma |
| High-sensitivity C-reactive protein | | hsCRP | Inflammation | Plasma |
| Homocysteine | | HMCys | Oxidative stress | Plasma |
| Glucose | | Gluc | Metabolic status | Plasma |
| Plasminogen activator inhibitor-1 | | PAI-1 | Coagulation | Plasma |
| Tissue plasminogen activator | | tPA | Coagulation | Serum |
| E-selectin | | SELE | Endothelial dysfunction | Plasma |
| Endothelin-1 | | ET-1 | Vascular tone/endothelial dysfunction | Serum |
| 3-nitrotyrosine | | 3-NTyr | Nitrosative stress/vascular tone | Plasma |

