Blood samples will be taken for the clinical laboratory panel. Details of all blood samples collected in this study are presented in Section 7.4.2.The following evaluations will be performed:

| **Serum biochemistry:** | **Units** | **Haematology:** | **Units** |
| --- | --- | --- | --- |
| Aspartate aminotransferase (AST) | IU/L | Haemoglobin | g/dL |
| Alanine aminotransferase (ALT) | IU/L | Haematocrit (packed cell volume [PCV]) | % |
| Alkaline phosphatase | IU/L | Total and differential leukocyte count | 10^9^/L & % |
| Gamma‑glutamyl transferase (GGT) | IU/L | Red blood cell (RBC) count | 10^12^/L |
| Sodium | mmol/L | Platelet count | 10^9^/L |
| Potassium | mmol/L | Mean cell volume (MCV) | fL |
| Chloride | mmol/L | Mean cell haemoglobin (MCH) | pg |
| Calcium | mmol/L | MCH concentration (MCHC) | g/dL |
| Inorganic phosphate | mmol/L | **Urinalysis:** | **Units** |
| Glucose | mmol/L | Microscopic examination | + |
| Urea | mmol/L | pH | NA |
| Uric acid | µmol/L | Specific gravity | NA |
| Total bilirubin | μmol/L | Protein | + |
| Direct bilirubin | μmol/L | Glucose | + |
| Creatinine | μmol/L | Ketones | + |
| Total protein | g/L | Bilirubin | + |
| Albumin | g/L | Blood | + |
| Total cholesterol | mmol/L | Nitrite | neg/pos |
| Triglycerides | mmol/L | Urobilinogen | + |
| Creatinine phosphokinase (CPK) | IU/L | Leukocytes | cells/field |
| Blood urea nitrogen (BUN) | mmol/L | Urine pregnancy test^d^ | neg/pos |
| **Serology^a^:** | **Units** | Urine drug screen^e^ | neg/pos |
| Hepatitis B surface antigen (HBsAg) | neg/pos | **Additional Tests** |  |
| Hepatitis C antibody | neg/pos | Alcohol breath test | neg/pos |
| Human immunodeficiency virus (HIV)^b^ | neg/pos |  |  |
| **Hormone Panel^c^:** | **Units** |  |  |
| Follicle‑stimulating hormone (FSH) | mIU/L |  |  |
| Human chorionic gonadotropin (hCG; serum pregnancy test) | IU/L |  |  |

^a^ Screening only
^b^ HIV1/2 and p24 antigen
^c^ In all females at Screening only
^d^ Female subjects only. A positive urine pregnancy test will be confirmed with a serum pregnancy test. See Schedule of Assessments in Appendix 15.1 for scheduled timepoints.
^e^ Urine drugs of abuse screen will be conducted for amphetamines, barbiturates, benzodiazepines, cocaine, ecstasy, methamphetamine, morphine, methadone, tricyclic antidepressants, and tetrahydrocannabinol.
neg = negative
pos = positive

- - 1. Urine Drugs of Abuse Screen and Alcohol Breath Test

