Subjects will be asked to provide urine samples for drugs of abuse screens at the times indicated in the Schedule of Assessments (Appendix 15.1). Urine samples will be screened for the presence of the following drugs of abuse: amphetamines, barbiturates, benzodiazepines, cocaine, ecstasy, methamphetamine, morphine, methadone, tricyclic antidepressants, and tetrahydrocannabinol.

Subjects will be screened for the presence of breath alcohol at the times indicated in the Schedule of Assessments (Appendix 15.1).

- - 1. Body Fat Analysis

Subjects’ body fat will be measured at the times indicated in the Schedule of Assessments (Appendix 15.1) using an OMRON BF511 machine according to the manufacturer’s instructions. The following parameters will be calculated:

- Body fat (%)
- Visceral Fat (up to 30 levels)
- BMI
- Skeletal Muscle (in %)

Body fat measurements will be taken at least 2 hours after meals.

- 1. Sample Collection for Biomarker and Exploratory Endpoint Assessments
     1. Exhaled Carbon Monoxide and Nitric Oxide

Exhaled carbon monoxide (CO) will be measured using the EC50 Micro III Smokerlizer (Bedfont) CO meter, or similar device. Exhaled NO will be measured using an Aerocrine NIOX VERO device. Subjects will not be allowed to use any study products/smoke any cigarettes or eat within 30 minutes prior to CO or NO level measurements. Subjects should also avoid all food and drink for 1 hour prior to NO measurements. Levels will be measured at the times indicated in the Schedule of Assessments (Appendix 15.1).

- - 1. Urinary BoE and BoBE

Spot urine samples will be used for the urine drugs of abuse screen, cotinine test, urine pregnancy test, and safety urinalysis.

Pooled 24-hour urine samples will be collected for analysis of urinary BoE and BoBE. Creatinine in urine will also be calculated and used to report BoBE as amount per unit of creatinine.

Samples will be transported and stored as detailed in Section 7.4.

- - 1. Blood Sampling for BoE, BoBE, and Exploratory Endpoints

Blood samples will be collected as described in the laboratory manual. Samples will be transported and stored as detailed in Section 7.4.

- 1. Sample Handling, Transport and Storage

All samples (urine and blood) will be transported on dry ice for analysis, with replicate samples being shipped independently.

- - 1. Urine Samples

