For BoE and BoBE analyses, urine samples will be collected over concurrent 24-hour time periods beginning on the day before each study visit. All urine voided during the 24‑hour period will be collected and samples aliquoted for the various analyses. The samples will be refrigerated at between 2°C to 8°C. Additional sample handling instructions will be provided in the laboratory manual.

The urine samples collected during a single 24-hour interval will be pooled together and weighed. The samples will be related to the day on which the 24-hour collection period ended. The pooled samples will be thoroughly mixed before providing aliquots for analyses. The total volume of all urine collected over each 24-hour period will be calculated from weight and specific gravity. Urine aliquots will be stored in suitably labelled tubes at the temperatures indicated in the laboratory manual pending assay.

- - 1. Blood Samples

Blood samples will be collected by qualified and trained site personnel. The following blood volumes will be withdrawn for each subject:

|  | **Volume per Blood Sample (mL)** | **Maximum Number of Samples** | **Total Amount of Blood (mL)** |
| --- | --- | --- | --- |
| Serum biochemistry and hematology^1^ | 7.5 | 7 | 52.5 |
| Serology | 3.5 | 1 | 3.5 |
| White blood cell count | 2.0 | 14 | 28.0 |
| s-ICAM1 | 4.0 | 10 | 40.0 |
| HDL and LDL | 2.0 | 14 | 28.0 |
| Cholesterol and triglycerides^2^ | 1.0 | 4 | 4.0 |
| CEVal (Hb adduct) | 10.0 | 7 | 70 |
| Other BoBE | 5.0 | 10 | 50.0 |
| Serum NMR lipoprotein and metabolomics, and plasma BH2/BH4 ratio | 18.0 | 6 | 108 |
| Transcriptomics (WBC) | 5.0 | 4 | 20.0 |
|  | | **Total:** | **404** |

Abbreviations: BH2/BH4 = dihydrobiopterin/tetrahydrobiopterin; BoBE = biomarker of biological effect; CEVal = N-(2-cyanoethyl)valine; Hb = haemoglobin; HDL = high-density lipoprotein; LDL = low-density lipoprotein; NMR = nuclear magnetic resonance; s‑ICAM1 = soluble intracellular adhesion molecule-1; WBC = white blood cell.
Blood samples will be destroyed as per the laboratory’s standard procedures.
^1^ Glucose, total cholesterol, and triglycerides will be measured as part of serum biochemistry assessments. Serum biochemistry tests include follicle-stimulating hormone and serum pregnancy tests.
^2^ Samples will be collected specifically for cholesterol and triglyceride assessment at Visits 2 and 3.

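### The dry-ice transport rule in Section 7.4 covers the whole-blood tubes for WBC count, a secondary endpoint that cannot be validly counted in frozen blood

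*Protocol*

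**What the plan says.** Section 7.4 of the protocol opens with the transport rule for the whole study: "All samples (urine and blood) will be transported on dry ice for analysis". It separates urine from blood only to say that both are covered. Whole blood, plasma and serum are not distinguished.

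Section 7.3.3, on blood for biomarkers of exposure, biomarkers of biological effect and exploratory endpoints, divides the task in two. Collection goes to the manual: "Blood samples will be collected as described in the laboratory manual". Transport and storage stay in the protocol: "Samples will be transported and stored as detailed in Section 7.4".

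The secondary endpoint table in Section 2.4.2 lists WBC count among the biomarkers of biological effect with its matrix: "White blood cell count | | WBC count | Inflammation | Whole blood". The row has no dagger, so WBC count belongs to the Section 9.3 comparisons. It also has its own row in the blood volume table of Section 7.4.2, giving volume per sample, maximum number of samples and total: "White blood cell count | 2.0 | 14 | 28.0".

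The safety haematology panel in Section 7.2.9 separately contains "Total and differential leukocyte count".

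**The concern.** Dry ice freezes what it carries. That suits urine, plasma and serum aliquots. A cell count needs intact cells, and freezing unpreserved whole blood breaks them open. For one listed endpoint the protocol therefore fixes a handling rule that defeats the measurement.

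This is more than detail left to a manual. Section 7.3.3 hands over collection but keeps transport, so a manual that ships WBC count tubes unfrozen would depart from the protocol as written, and one that follows the protocol would yield unusable tubes. A lost count cannot be recovered later. At stake is a secondary inflammation marker and its early time course.

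**Working it through.** No figure in the plan needs recomputing. The check sets the sections against each other and counts scheduled samples.

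**1. Does the rule reach the WBC count tube?** WBC count is a biomarker of biological effect (Section 2.4.2). Blood for those biomarkers is sent to Section 7.4 for transport (Section 7.3.3). Section 7.4 prescribes dry ice and names no exception. So it does.

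**2. Are these tubes in the shipped set?** The table divides the maximum samples in Section 7.4.2 by the scheduled timepoints in Appendix 15.1.

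| Blood sample | Maximum samples | Timepoints | Per timepoint |
| --- | --- | --- | --- |
| WBC count | 14 | 7 | 2 |
| HDL and LDL | 14 | 7 | 2 |
| s-ICAM1 | 10 | 5 | 2 |
| Other biomarkers of biological effect | 10 | 5 | 2 |
| CEVal | 7 | 7 | 1 |
| Serum biochemistry and haematology | 7 | 7 | 1 |

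Two WBC count tubes per visit fit the statement in Section 7.4 that replicates are shipped independently. This is an inference from a maximum. One tube per timepoint does not show local analysis either: CEVal is also drawn singly and is also under Section 7.3.3. The pattern is suggestive for WBC count and inconclusive for haematology.

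**3. Is there another leukocyte count?** WBC count is scheduled at Visits 1, 2, 3, 4, 7, 10 and 13. Clinical laboratory evaluations, which include haematology, fall at Screening, Visits 1, 4, 7, 10 and 13, and Follow-up. The overlap is Visits 1, 4, 7, 10 and 13, so 7 − 5 = 2 visits (Visits 2 and 3, Days 30 and 60) depend on the dedicated tube alone.

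**4. How many subject-visits is that?** Visits 2 and 3 apply to Arms A, B and D only. At full planned enrolment, 65 + 200 + 190 = 455 subjects, and 455 × 2 = 910 subject-visits. For the intended minimum of completers, 3 × 50 = 150, and 150 × 2 = 300. True attendance at these early visits would lie between these if the plan holds.

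**5. Where does WBC count enter the tests?** Section 9.3 compares Arm B with Arm A on secondary endpoints only if a primary endpoint is significant. At Day 90 it limits secondary testing to biomarkers of exposure, which WBC count is not. Its formal comparisons are therefore at Days 180 and 360 (Visits 7 and 13), adjusted for Visit 1. All three visits have a haematology panel. Visits 2 and 3 bear on the exploratory time-course objectives and the descriptive summaries.

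**The case against.** The strongest reply is that the word covering all samples cannot be literal. Urine drug, cotinine and pregnancy tests are done on spot urine at Visit 1 before randomisation or enrolment (Sections 6.2 and 7.3.2), and these cannot sensibly go on dry ice. Section 13.4 treats specimens that need frozen storage as a class of their own. The protocol never says where cell counts are run, and the laboratory manual may give workable handling. On this view Section 7.4 is a loosely worded courier sentence for biomarker aliquots.

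Much of that stands: this is probably over-general wording rather than actual practice. It does not clear the WBC count tube, because Section 7.3.3 sends that tube to Section 7.4 explicitly and the manual is given collection only.

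Two stronger readings are tempting. A reader might infer that WBC count could not be measured at any visit. The documents do not support this, because a leukocyte count is also part of haematology at five of the seven visits. A reader might also infer that haematology safety monitoring fails. That would rest on the word for all samples and on a pointer from Section 7.2.9 to Section 7.4.2, which holds the blood volumes. Section 7.2.9 has no transport cross-reference, and haemoglobin concentration survives lysis in any case.

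**Conclusion.** The rule is wrong as written for the dedicated WBC count tubes. If it were followed, they could not give a valid count at any of the seven visits where they are drawn. At Visits 2 and 3 that would leave no leukocyte count. At Visits 1, 4, 7, 10 and 13 the haematology panel would still supply one if its tubes are not frozen, which the protocol does not make clear. The protocol also does not say that the panel result may stand in for the endpoint.

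The effect is limited. No primary endpoint is a cell count, so the primary endpoints, alpha and sample size are untouched. The WBC count comparison is conditional, and its formal timepoints all have a haematology draw. A total of affected tubes across the study should not be inferred: it would assume full attendance and treat a maximum sample number as actual duplicates.

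The conclusion rests on two assumptions. One is general laboratory knowledge, not stated in the protocol, that freezing unpreserved whole blood lyses cells. The other is that the sites would follow Section 7.4 as worded.

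**What to change.** In Section 7.4, limit the dry-ice sentence to samples intended for frozen analysis: urine, plasma and serum aliquots, and any other samples so designated in the laboratory manual. Add one sentence saying that whole blood for cell counts, meaning both WBC count and haematology, is not frozen and is handled and counted as the laboratory manual specifies. Confirm that the manual agrees.

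This takes one or two sentences and adds no visits, blood volume or analyses. The small downside is a separate unfrozen shipment for the cell-count tubes, or counting them locally.

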1. ADVERSE EVENTS
   1. Definitions
      1. Adverse Events

The FDA modified risk tobacco product (MRTP) guidelines^26^ specify the following definition for AEs for tobacco products: an AE is any health-related event associated with the use of tobacco product in humans, which is adverse or unfavourable, whether or not it is considered related to the tobacco product, as defined by the MRTP guidelines.

An AE is defined as any untoward medical occurrence in a subject administered a study product, which does not necessarily have a causal relationship with the study product. An AE can therefore be any unfavourable and/or unintended sign (including an abnormal laboratory finding), symptom or disease temporally associated with the use of a study product, whether or not related to the study product.

- - 1. Serious Adverse Events

The FDA MRTP guidelines^26^ specify the following definitions for SAEs for tobacco products:

- results in death
- is life threatening
- requires inpatient hospitalisation or prolongation of existing hospitalisation
- results in persistent or significant disability/incapacity (disability is defined as a substantial disruption of a person’s ability to conduct normal life functions)
- is a congenital anomaly/birth defect

An important medical event that may not result in death, be life threatening or require hospitalisation may be considered a serious adverse experience when, based upon appropriate medical judgement, it may jeopardise the subject or may require medical or surgical intervention to prevent one of the outcomes listed in this definition. Examples of such medical events include allergic bronchospasm requiring intensive treatment in an emergency room or at home, blood dyscrasias or convulsions that do not result in inpatient hospitalisation, or the development of dependency or abuse.

Instances of death or congenital abnormality, if brought to the attention of the Investigator or their appropriately qualified designee at any time after last product use and considered by the Investigator or their appropriately qualified designee to be possibly related to the study product, will be reported to the Sponsor.

Definition of Life Threatening

An AE is life threatening if the subject was at immediate risk of death from the time of the event as it occurred; i.e. it does not refer to an event that might have caused death if it had occurred in a more serious form.

Definition of Hospitalisation

Adverse events requiring hospitalisation should be considered serious. In general, hospitalisation signifies that the subject has been detained (usually involving an overnight stay) at the hospital or emergency ward for observation and/or treatment that would not have been appropriate at the clinical site. When in doubt as to whether hospitalisation occurred or was necessary, the AE should be considered serious.

Hospitalisation for elective surgery or routine clinical procedures, which are not the result of an AE, need not be considered AEs and should be recorded on a clinical assessment form and added to the eCRF. If anything untoward is reported during the procedure, this must be reported as an AE and either ‘serious’ or ‘non-serious’ attributed according to the usual criteria.

- 1. Assessment of Adverse Events

The condition of each subject will be monitored from the time of signing the ICF, to Check‑out at the Follow-up Visit. In addition, any signs or symptoms will be observed and elicited at each visit by open questioning, such as “How have you been feeling since your last visit ?”

Subjects will also be encouraged to spontaneously report AEs occurring at any other time during the study.

Any AEs and remedial action required will be recorded in the subject's source data. The nature, time of onset, duration and severity will be documented, together with the Investigator’s opinion of the relationship to product use.

Any clinically significant abnormalities identified during the course of the study will be followed-up until they return to normal or can be clinically explained.

- 1. Intensity of Adverse Events

The causal relationship between an AE and the study product is defined as follows:

**Not Related** The AE is definitely caused by the subject's clinical state or the study procedures/conditions.

**Unlikely Related** The temporal association between the AE and the product is such that the product is not likely to have any reasonable association with the AE.

**Possibly Related** The AE follows a reasonable temporal sequence from the time of product use but could have been produced by the subject's clinical state or the study procedures/conditions.

**Related** The AE follows a reasonable temporal sequence from the time of product use, abates upon discontinuation of the product and reappears when the product is reintroduced.

The severity of an AE will be recorded as one of the following:

**Mild** Easily tolerated; does not interfere with normal daily activities; does not require intervention

**Moderate** Causes some interference with daily activities; minimal, local or non‑invasive intervention indicated

**Severe** Medically significant event; daily activities limited or completely halted; hospitalisation or prolongation of hospitalisation indicated

Every reasonable effort will be made to follow-up subjects who have an AE at Follow-up, if possible, until resolution.

Any AE assessed as related to the study product will be assessed for its expectedness. An AE will be regarded as ‘unexpected’ if its nature or severity is not consistent with information already known about the study product, and is not listed in the current Investigator’s Brochure (IB).^19^ The IB provides further detail on signs or symptoms that might be expected with the use of the study product, including information relating to malfunction or misuse.

- 1. SAE Reporting

All AEs occurring during this clinical study will be recorded from time of the subject signing the ICF until the end of the study. The Investigator or their appropriately qualified designee will review each event, grade its severity and assess its relationship to the product consumption and/or the study procedures. The date of onset, time of onset, and outcome of each event will be noted.

If any of the above AEs are serious, special procedures will be followed. The Investigator will report all SAEs to the Covance Pharmacovigilance and Drug Safety Services Department within 24 hours. This information must be sent by fax by filling out the serious AE form. Written reports must then be submitted within 48 hours, whether or not the serious events are deemed related to study procedures or products. The EC will be notified by these reports.

If an SAE occurs during this study, the Medical Monitor will be contacted.

- - 1. Abnormal Results of Laboratory Tests

Any clinical safety laboratory results that are outside of the normal reference range will be reviewed for clinical significance by the Investigator or their appropriately qualified designee. If the abnormal result is considered to be of clinical significance, it will be recorded as a concomitant disease (prior to enrolment) or an AE (after enrolment). As for other AEs, the relationship to the study product, intensity, seriousness and outcome of abnormal clinical safety laboratory results will be recorded.

- - 1. Abnormal Results of Other Tests and Investigations

Any ongoing medical conditions or clinically relevant findings detected at Screening will be considered to be a concomitant disease and the subject’s eligibility to participate in the study will be reviewed. Any new, clinically relevant, abnormal findings or worsening of pre‑existing conditions detected during the study after the Screening Visit until the end of the study will be documented as an AE.

- 1. Reporting and Follow-up of Pregnancies

For pregnancies detected during the Screening Period and prior to first product use, the subject will be considered a screening failure and removed from the study. The diagnosed pregnancy will be captured on the screening failure eCRF.

All pregnancies occurring after signing the ICF and diagnosed after enrolment until the completion of the study must be reported to the Investigator. Any pregnancy potentially associated to exposure to the study product, including pregnancies spontaneously reported to the Investigator or their appropriately qualified designee after the end-of-study must be reported and followed-up. Potential association with exposure to the study product is defined as the conception date being calculated before the last exposure to the study product.

The Investigator will complete a Pregnancy Form for all pregnancies (including positive urine pregnancy tests). Pregnancies must be reported to the Medical Monitor, according to their standard procedures.

- 1. Adverse Events Leading to Withdrawal

Subjects who are withdrawn from the study because of an AE will undergo the following assessments and will return for a Follow-up Visit:

- Physical examination (symptom driven)
- Vital signs
- 12-lead ECG
- Review of AEs/SAEs
- Lung function tests
- Clinical laboratory evaluations
- Urine pregnancy test (female subjects only)

The Investigator will follow-up any AE until they have resolved, stabilized or an acceptable explanation has been found.

- 1. Investigational Product Misuse

Any occurrence of THP misuse by a subject will be documented by site staff. Misuse is defined as actions not in accordance with the product instructions.

Investigational product misuse may result in use-related hazards.

Use-related hazards are derived from the US FDA Medical Device Use Safety Guidance:^27^

- Hazards caused specifically by how a device is used.
- Unanticipated use scenarios (e.g. applying any chemicals, using conventional cigarettes, mechanical damage of the product) that result in hazards must be documented and reported by the Investigator.

According to FDA Medical Device Regulation, data should be collected regarding the use‑related hazards that have occurred with the device and when information pertaining to device use safety is extensive, it is helpful to provide it in summary form that highlights the most important issues, considerations, resolutions, and conclusions. The level of detail of device use documentation submitted should be consistent with the level of concern of use‑related hazards for the device.

- 1. Investigational Device Malfunctions

Subjects will be provided with 2 identical devices which may be used concurrently. Subjects should report any device malfunctions, loss, or damage immediately to the site.

Any occurrence of malfunction of the THPs will be documented by the site staff and reported to the Sponsor as appropriate. Any apparently malfunctioning device will be removed from use and replaced.

